### Cardiometabolic assessments

Fasting blood samples will be obtained at 6 am, within 24 hours after hospital referral, and directly sent to accredited laboratories at the Bern University Hospital to be processed within clinical routine on the same day. For catecholamine and cytokine analyses, ethylene-diamine-tetraacetic acid (EDTA) samples are centrifuged once at 2,000 g for ten minutes at room temperature; obtained plasma is frozen in CryoPure Tubes (Sarstedt, Numbrecht, Germany) at -80°C until analysis.

A Modular P800 system with ion selective electrodes and Cobas standard test kits (all Roche Diagnostics, Rotkreuz, Switzerland) will be used to determine levels of blood lipids, glucose, alanine transaminase, and creatinine from heparin plasma samples. Hemoglobin A1c will be determined in whole blood using high-performance liquid chromatography on a HLC-723 G7 analyzer (Tosoh Corp., Tokyo, Japan). Hemoglobin, hematocrit, leukocyte and thrombocyte counts will be determined from EDTA plasma samples using the LH 750 analyzer (Beckman Coulter, Miami, FL, USA).

Heparin plasma samples will be analyzed for high-sensitivity C-reactive protein by a latex particle immunoturbidimetric assay on the Roche Modular P800 analyzer (Roche Diagnostics, Rotkreuz, Switzerland). Levels of tumor necrosis factor-α, interleukin-6, and interleukin-4 will be measured in EDTA plasma samples using luminex technology (Bio-Plex Pro™ Cytokine Assays, Bio-Rad Laboratories AG, Cressier, Switzerland).

Hemostasis markers will be determined from citrate plasma samples. Fibrinogen clotting activity will be measured by the Clauss method on a Behring Coagulation system automated analyzer using commercial reagents and standard human plasma (Dade Behring AG, Düdingen, Switzerland). D-dimer levels will be determined through an enzyme-linked immunosorbent assay (Vidas-D-Dimer, bioMérieux, Geneva, Switzerland). A quantitative, automated immunoassay will be used to determine von Willebrand factor antigen (Siemens, Marburg, Germany).

Serum cortisol will be measured by competitive immunoassay using Roche Modular E170 (Roche Diagnostics, Rotkreuz, Switzerland). Norepinephrine and epinephrine concentration will be determined from EDTA plasma samples by means of HPLC and electrochemical detection after liquid-liquid extraction [78].

Heart rate and frequency domain measures of heart rate variability will be assessed from five-minute electrocardiogram recordings with the Finometer using customized software (TPD Biomedical Instruments, Amsterdam, The Netherlands) and averaged across the recording period. Blood pressure will be measured twice with an interval of ten minutes with the automatic Omron M6W Blood Pressure Monitor (Omron Healthcare Europe BV. Hoofddorp, The Netherlands); the average systolic and diastolic blood pressure will be computed for analysis.

The hip circumference measurement will be taken around the widest portion of the buttocks. The waist circumference will be measured at the approximate midpoint between the lower margin of the last palpable rib and the top of the iliac crest. The measurement of body weight will be performed with participants wearing no shoes and light clothing to the nearest 0.1 kg with a digital balance (Modell W41, Firma Migros, Switzerland) at follow-up assessments, and to the nearest 0.5 kg by history at hospital referral, because of potential fluid overload. Height will be measured with a reference tape to the nearest 0.1 cm. Body mass index will be calculated by dividing the weight in kilograms by height in meters squared.

### Ethical considerations

The study complies with the declaration of Helsinki. The ethics committee of the State of Bern, Switzerland, approved the study protocol. All potentially eligible patients (that is, those meeting the inclusion criteria) receive written information about the aim of the study, benefits and risks of participation and the exact study procedure before giving their written informed consent to participate in the study that includes two follow-up assessments. All participants are informed that they can withdraw themselves from the study anytime. All patients are encouraged to first contact their primary care physician in case they feel a need for mental health treatment at any time during follow-up. However, these patients will remain in the study, as it would be highly unethical to ask them to refrain from seeking professional help during follow-up. Patients who are diagnosed with syndromal PTSD at follow-up investigations are told their diagnosis. Moreover, patients and their primary care physicians are informed about the possibility of a referral to the Department of Clinical Psychology and Psychotherapy, University of Bern, Switzerland to receive treatment for PTSD.

To identify adverse reactions to the *verum* intervention, two interim safety analyses will be performed after subgroups of 130 and 260 patients on the primary efficacy endpoint, that is, interviewer-rated posttraumatic stress level at three months after the intervention. The spending function approximating O’Brien-Fleming boundaries [79] will be used to determine criteria for the interim and final analyses to protect the overall false positive rate of the trial at *P* = 0.05. The study will be stopped for inequality in outcome between the *verum* and control group if results reach a predefined level of statistical significance at the two-sided alpha level of 0.001 and 0.014, respectively. The nominal two-sided significance level for the final evaluation will be 0.045. This provides us with a 3.3% and 44.2% chance of stopping the trial after the first or second interim analysis, respectively.

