The primary aim of our randomized-controlled trial is to examine whether the development of posttraumatic stress can be reduced by a single counseling session of 45 minutes targeting MI-triggered traumatic reactions (that is, the *verum* intervention). The effect of this counseling session will be tested against a control intervention targeting the general role of psychosocial stress in CHD. The verum and control interventions are both administered to patients at high risk to develop PTSD within a setting of a coronary care unit (CCU) within 48 hours by the bedside after patients having reached stable circulatory conditions. Secondary aims of our trial are to investigate psychosocial functioning and cardiometabolic risk markers between the two active intervention arms.

Our main hypothesis is that trauma-focused psychological counseling is more effective than non-trauma focused counseling for reducing posttraumatic stress after acute MI. Specifically, we predict that compared with the control group, the verum group will report at least 20% lower posttraumatic stress levels at three months after MI as rated by blinded interviewers (primary outcome). We expect that this group difference will persist for up to 12 months. Compared to the control group, the verum group will additionally show better psychosocial functioning and a more favorable profile of cardiometabolic risk markers after 3 and 12 months of follow-up (secondary outcomes).

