### Sample size calculation

As opposed to the primary outcome, which is interviewer-rated posttraumatic stress, the sample size calculation is based on self-rated posttraumatic stress levels, which we had previously collected from almost 300 post-MI patients [12]. Based on these data we expect that patients at a high risk to develop PTSD (compare to below for definition) will show a mean score of 15.2 ± 10.1 (range 0 to 51) on the self-rated Posttraumatic Diagnostic Scale (PDS) at three months after MI. However, we cannot exclude a non-specific beneficial effect of the control intervention on PTSD symptom development. Therefore, we assume that patients in the control group will decrease their posttraumatic stress level by 1.0 PDS score point to 14.2 score points. We defined a 20% decrease in the posttraumatic stress level in the *verum* group compared to the control group to be clinically meaningful. Therefore, in order to achieve a 20% difference in posttraumatic stress levels between the *verum* intervention and the control group, the *verum* intervention should achieve a reduction of 3.9 PDS score points from 15.2 to 11.3 to show a clinically meaningful effect. Applying an alpha error level of *P* = 0.05, a beta error level of 20% and a group difference in the total PDS score of 2.9 ± 10.1, the sample size to detect a significant difference of 20% in posttraumatic stress levels between groups is n = 194 per group. Because of possible drop outs (including post-MI mortality), we will oversample each group by 10% (that is, n = 213 per group), yielding a total sample of n = 426 eligible post-MI patients to be randomly allocated to the two active intervention arms.

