### Statistical analyses

Data will be analyzed using the latest version of the Statistical Package for the Social Sciences (SPSS Inc. Chicago, IL, USA) with a significance level of *P* < 0.05 (two-tailed). Before analysis, all outcome variables will be tested for normality by the Kolmogorov-Smirnov test and, if necessary, transformed to obtain a normal distribution. Differences in variables between the two intervention groups will be calculated using the *t*-test for continuous data and the chi-squared test for categorical data. The primary outcome is the severity of posttraumatic stress levels rated by the CAPS interview at the three-month follow-up. Secondary outcomes are measures of psychosocial functioning and cardiometabolic biomarkers at three months follow-up (primary analysis). Key secondary outcomes are quality of life, plasma levels of C-reactive protein, D-dimer, cortisol and norepinephrine, as well as high-frequency heart rate variability. These outcomes are important indicators of mental health functioning, low-grade inflammation and coagulation activity as well as hypothalamic-pituitary adrenal axis and autonomic nervous system function. Repeated measures analysis of variance will be applied to test for a change in posttraumatic stress levels and in measures of psychosocial functioning and cardiometabolic biomarkers between the two follow-up visits (secondary analysis). The relative risk for developing a diagnosis of PTSD during follow-up in the control group compared to the *verum* group will be calculated by means of logistic regression analysis. For a complementary sensitivity analysis, we will apply univariate, multivariate and repeated measures analysis of covariance taking into account sociodemographic, medical and psychosocial covariates, and received psychotherapy during follow-up.

Missing values for questionnaire items will be replaced using the expectation maximization algorithm [80]. If patients drop out during follow-up, we will carry forward the last observed data points to impute missing endpoints. Randomized patients who will not undergo the intervention are excluded from the analysis. However, we will perform an additional analysis based on the intention-to-treat principle with all randomized patients.

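### The interim stopping rule corrects the significance levels but not the effect estimate: on the planning figures the unadjusted reduction is about 9% too high on average, and averages about 30% against a true 20% after an early stop for benefit

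*Protocol article*

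**What the plan says.** The Ethical considerations section of the protocol article sets two interim analyses, after 130 and 260 patients, on the interviewer-rated (CAPS) stress level at three months. They are labelled safety analyses, but the rule works in both directions: "The study will be stopped for inequality in outcome between the *verum* and control group if results reach a predefined level of statistical significance". The two-sided levels are 0.001 and 0.014, with 0.045 at the end, to hold the overall false positive rate at 0.05. The section adds: "This provides us with a 3.3% and 44.2% chance of stopping the trial after the first or second interim analysis, respectively".

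The Statistical analyses section describes the group comparison without reference to these looks: "Differences in variables between the two intervention groups will be calculated using the *t*-test for continuous data".

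The size of the effect is part of the claim. The hypothesis in the Background is that "the verum group will report at least 20% lower posttraumatic stress levels at three months after MI as rated by blinded interviewers". The Sample size calculation section gives the threshold its meaning: "We defined a 20% decrease in the posttraumatic stress level in the *verum* group compared to the control group to be clinically meaningful".

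**The concern.** Spending the type I error correctly makes the test valid. It does not make the ordinary mean difference an unbiased estimate. A trial that stops because the observed difference is large keeps the high estimates, and a trial that continues dilutes its early high values with later data. Taken together, the stopping rule and the t-test as stated yield an effect size that is too high on average and an ordinary interval that lies too high.

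This matters more here than in a trial that only asks whether the arms differ. Readers will set the reported percentage reduction against the plan's own 20% mark, and the plan itself considers an early stop quite likely.

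**Working it through.** **Inputs.** From Sample size calculation: "a group difference in the total PDS score of 2.9 ± 10.1"; control patients "decrease their posttraumatic stress level by 1.0 PDS score point to 14.2 score points"; 194 per group. From Ethical considerations: looks at 130 and 260 patients, which is 65 and 130 per arm with 1:1 allocation; two-sided levels 0.001, 0.014 and 0.045. **Assumption:** the mean and SD are PDS values. The article gives none for CAPS, on which stopping is judged, so PDS stands in for it.

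**The plan's own figures first.**
- Sample size: 2 × (1.960 + 0.842)² × 10.1² / 2.9² gives 191 per arm, close to the stated 194.
- Standard error of the difference, 10.1 × √(2/n): 1.772 at 65, 1.253 at 130 and 1.025 at 194 per arm.
- Three-look O'Brien-Fleming boundaries are z = 3.471, 2.454 and 2.004, with two-sided p = 0.0005, 0.0141 and 0.0451. These match the stated levels after rounding.
- Chance of crossing at a true 2.9: 1 − Φ(3.471 − 2.9/1.772) = 3.3% at look 1 and 1 − Φ(2.454 − 2.9/1.253) = 44.5% at look 2. The stated 3.3% and 44.2% are thus reproduced. The second figure is in effect the cumulative chance of an early stop; stopping at look 2 itself is about 40 to 41%.

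**Boundary on the effect scale** (stated levels; z × SE, as a share of 14.2):
- Look 1: 3.291 × 1.772 = 5.83 points, 41.1%.
- Look 2: 2.457 × 1.253 = 3.08 points, 21.7%.
- Final: 2.005 × 1.025 = 2.06 points, 14.5%.

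The look-2 figure equals 2.457 × √(2/130) × SD/mean = 0.305 × SD/mean. It is 21.7% at the PDS ratio of 10.1/14.2 = 0.711, about 18% at a ratio of 0.6 and about 30% at 1.0. It falls below 20% when the ratio is below about 0.66.

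**Simulation of the design** with the stated levels (at least 1.5 million trials per true effect). Overall type I error is 0.050 and power at 2.9 is 80%.

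| True reduction | Chance of early stop | Mean unadjusted reduction after a stop for benefit | Share of these stops above the truth |
|---|---|---|---|
| 1.42 points (10%) | 9.4% | 3.82 points (26.9%) | 100% |
| 2.0 points (14%) | 19.6% | 3.94 points (27.7%) | 100% |
| 2.9 points (20.4%) | 44.5% | 4.21 points (29.7%) | 100% |
| 25% | 65% | 31.7% | 78% |
| 30% | 83% | 34.7% | 62% |

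Over all trials at a true 2.9, the mean estimate is 3.15 points, so the bias is 0.25/2.9 = 9%. The nominal 95% interval covers about 93.8% and lies wholly above the truth in about 3.8% of trials instead of 2.5%. Trials that run to the end average (3.15 − 0.445 × 4.21)/0.555 = 2.30 points, so the bias goes the other way there.

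**What an adjustment does.** The bias-adjusted mean is the true difference whose expected estimate under the design equals the observed one. It maps 3.5 to 3.22 and 4.0 to 3.68. At a true 2.9 it brings the all-trial mean from 3.15 to 2.92 and the root mean squared error from 1.34 to 1.24. After an early stop for benefit the mean only falls from 4.21 to about 3.90 points (27.5%), and over 99% of these trials still read 20% or more.

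**The case against.** The strongest objection is that the article is silent on estimation rather than wrong. It names a t-test, mentions no confidence interval for the primary effect, and does not say which estimate would be published after a stop. A condensed article may leave that to the full protocol or the analysis plan. This stands in part: the article does not commit the sponsor to an unadjusted interval. But it does state both halves, a detailed stopping rule and a t-test with no link to it, and followed as written they give a biased value for the quantity named in the hypothesis.

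Second, a reader might infer that every early stop must overstate the benefit and must show at least 21.7%, so that the 20% mark is passed by construction. The documents do not support this, for four reasons:
- For true effects above about 22%, many stops do not overstate (see the table).
- The 21.7% rests on PDS figures, while the rule acts on CAPS.
- Outcomes may be transformed before testing, and a boundary on a transformed scale fixes no raw percentage.
- At the planned accrual, 426/24 × 3 = about 53 further patients would be randomised before the 260th reaches three months. If their data entered the estimate, the mean after a stop would be 3.94 rather than 4.21 points at the planned effect, and about 8% of early stops would read below 20%.

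Third, no section makes success depend on the observed reduction reaching 20%. It is a prediction and a planning target. That is correct and limits the consequence to interpretation.

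Fourth, adjustment leaves most of the inflation after a stop in place. That is also correct, so the fix has to say so.

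**Conclusion.** The point holds in limited form. Error control is sound, but the planned comparison ignores the stopping rule when it comes to the size of the effect. On the planning figures, with CAPS assumed to behave like PDS and the stated looks and levels, the unadjusted estimate is about 9% too high over all trials (3.15 against 2.9) and the nominal 95% interval covers about 93.8%. That average distortion is modest. The larger one is conditional: if the planned effect is true, about 44% of trials stop early for benefit and their unadjusted reduction averages about 30% against a true 20%. The 44% applies only at the planned effect; it is about 9% at a true 10% reduction. The 21.7% at the second look is an illustration from PDS figures, not a known floor for CAPS.

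**What to change.** Add to the Statistical analyses section, in substance:
- The primary effect is reported with an estimate and confidence interval that account for the group-sequential design, for example the bias-adjusted mean, with the unadjusted difference beside it.
- Any statement about a 20% reduction refers to the adjusted estimate.
- After an early stop the effect size is to be read with caution, because the adjustment removes the average bias but only a small part of the inflation given a stop (about 4.2 to 3.9 points at a true 2.9).

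The estimator should be named before the first interim look. The cost is a few sentences, a short calculation outside the standard t-test output, and a slightly less favourable reported effect: 3.5 becomes 3.22 and 4.0 becomes 3.68, a reduction of about 8%. No extra patients or visits are needed.

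### The first-look stopping level is printed as 0.001, but the stated 3.3% chance of stopping belongs to a level of about 0.0005; the 44.2% is cumulative but not labelled so

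*Protocol article*

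**What the plan says.** Everything on this point stands in the last paragraph of Ethical considerations, except the effect size and group size, which are under Sample size calculation.

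- Looks: "two interim safety analyses will be performed after subgroups of 130 and 260 patients on the primary efficacy endpoint".
- Boundary: "The spending function approximating O’Brien-Fleming boundaries [79] will be used to determine criteria for the interim and final analyses", with the aim "to protect the overall false positive rate of the trial at *P* = 0.05".
- Interim rule: the trial stops if "results reach a predefined level of statistical significance at the two-sided alpha level of 0.001 and 0.014, respectively".
- Final analysis: "The nominal two-sided significance level for the final evaluation will be 0.045".
- Consequence: "This provides us with a 3.3% and 44.2% chance of stopping the trial after the first or second interim analysis, respectively".
- Planning effect: "a group difference in the total PDS score of 2.9 ± 10.1", with 80% power and 194 per group before the allowance for dropout.

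The article does not say that 0.001 is a rounded value, whether 44.2% is cumulative, or under which true difference the two chances were calculated.

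**The concern.** A stopping level and the chance of crossing it are tied together once the effect, the SD and the number of patients at the look are fixed. The protocol gives all of these, so the printed chances can be checked against the printed levels. At the first look they do not agree: 0.001 gives a visibly larger chance than 3.3%.

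The level is also an operative rule as well as a description. A first-look P value between about 0.0005 and 0.001 stops the trial under the written level, but would not stop it under the boundary that produced the 3.3%.

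The second figure raises a question of label. The words 'or' and 'respectively' pair each percentage with one look, so a reader can take 44.2% as the second look's own chance, which it is not.

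**Working it through.** **Inputs.** Difference 2.9 and SD 10.1, 80% power, 194 per group (Sample size calculation); 1:1 allocation (Design); looks at 130 and 260 patients, so 65 and 130 per arm; two-sided levels 0.001, 0.014 and 0.045; overall alpha 0.05 (Ethical considerations).

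**Step 1: reproduce the plan's figures.** Take a classical two-sided O'Brien-Fleming design with three equally spaced looks, overall alpha 0.05 and 80% power, evaluated by numerical integration over the looks.

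| | Look 1 | Look 2 | Final |
|---|---|---|---|
| Critical z | 3.471 | 2.454 | 2.004 |
| Nominal two-sided level | 0.00052 | 0.0141 | 0.0451 |
| Level as printed | 0.001 | 0.014 | 0.045 |
| Chance of stopping at this look | 3.29% | 40.95% | – |
| Chance of having stopped by this look | 3.29% | 44.24% | – |

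The expected z at full information (the drift) that gives 80% power is 2.826. The size per arm is then 2 × (10.1 × 2.826 / 2.9)² = 193.7, which rounds up to the printed 194. A third and two thirds of 388 are 129.3 and 258.7, close to the printed 130 and 260. Levels, chances and sample size therefore all come from this one design, with 44.2% as the cumulative figure.

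A Lan-DeMets spending function of O'Brien-Fleming type at the same thirds gives levels 0.0002, 0.0120 and 0.0463 and cumulative chances of 1.9% and 41.7%. It matches neither the printed levels nor the printed chances.

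**Step 2: apply the printed first-look level.** Expected z at a look with n per arm = 2.9 / (10.1 × √(2/n)).

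- n = 65: 2.9 / (10.1 × √(2/65)) = 1.637.
- Level 0.001, critical z 3.2905: P(N > 3.2905 − 1.637) = 4.9%.
- Level 0.0005, critical z 3.4808: P(N > 3.4808 − 1.637) = 3.3%.
- Level 0.00052: also 3.3%.

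The chance of crossing on the opposite side is negligible under this difference. With the t distribution instead of the normal, 0.001 gives 4.6% and 0.0005 gives 3.0%, so the gap remains.

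**Step 3: the second look.** Using 130/260/388 patients and 194 per arm at the end:

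| First-look level | Look 1 | Look 2 alone | By look 2 | Power | Overall alpha |
|---|---|---|---|---|---|
| 0.001 (as printed) | 4.9% | 39.6% | 44.5% | 80.0% | 0.0500 |
| 0.0005 | 3.3% | 41.2% | 44.4% | 80.0% | 0.0498 |

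With looks at exact thirds and the printed 0.001, the overall alpha is 0.0501 and the cumulative chance 44.3%. Under either first-look level, 44.2% fits the cumulative chance and is 3 to 5 points above the second look's own chance.

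**The case against.** The strongest reply is that nothing was miscalculated. The classical O'Brien-Fleming levels round to exactly the three printed levels, and the same design yields 3.3%, 44.2% and 194 per group. The article names the boundary family, so a statistician can recover the unrounded value. As printed, 0.001 is unambiguous, no competing rule appears, and it holds the overall error rate at 0.050. Under the planned effect the two thresholds lead to different first-look decisions in only about 1.6% of trials (4.9% − 3.3%). Group-sequential output is often given cumulatively, and the sentence can be read so.

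Most of this stands, and it rules out some stronger readings. A reader might infer that the design or its error control is faulty; Step 1 and the alpha and power columns show otherwise. A reader might add the two percentages to 47.5%, but that sum appears nowhere in the article and follows only if 44.2% is taken as the second look alone. A reader might also take the percentages as a measure of protection against harm, because the looks are introduced as safety analyses. The sentence makes no such claim, and the rule it follows is a two-sided one for a difference in either direction. Operating characteristics under no difference or under harm may be left to the full protocol or analysis plan, and their absence here is no fault.

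The reply does not remove two things. The printed level, used as written, does not give the printed 3.3%. And nothing in the sentence signals that the second figure is cumulative.

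**Conclusion.** The point holds as a minor correction. The first-look threshold was rounded from about 0.0005 to 0.001, roughly doubling it, while the chance beside it was left at the unrounded value: 4.9% against the stated 3.3%, a gap of 1.6 percentage points. The 44.2% is right as a cumulative chance and lacks that label; the second look's own chance is about 40-41%.

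The rounding explanation is inferred from the exact match in Step 1; the article does not state it. All the percentages assume a true difference of 2.9 with SD 10.1 and 65, 130 and 194 evaluable patients per arm. Those planning values are on the self-rated PDS, whereas the interim test is on the interviewer-rated CAPS, so they carry over only if the standardised difference is the same on both scales.

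**What to change.** Before the first look, make the level and the chance agree in one of two ways:

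- print the first-look level as 0.0005 and keep 3.3%; or
- keep 0.001 and restate the first-look chance as 4.9%.

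In both cases reword the second figure as a chance of about 44% of having stopped by the second look, and say that both chances assume the planned 2.9-point difference.

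The cost is one or two corrected sentences. Sample size, timing of the looks, the second-look and final levels, overall alpha (about 0.05) and power (about 80%) stay as they are under either choice. The choice should be recorded before any interim data are seen, because a first-look P value between 0.0005 and 0.001 would be handled differently.
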